## **6.6 OTHER MEDICATIONS**

### **6.6.1 Non-investigational medicinal products**

There is no current standard medical treatment option for the management of preeclampsia, however antihypertensive and other routine medication(s) (e.g. labetalol, nifedipine, methyldopa, hydralazine, magnesium sulphate, folic acid, iron supplementation etc.) will be concurrently ordered for the management of this patient cohort.

### **6.6.2 Permitted medications**

As outlined in the manufacturer's Product Information (*Appendix 1*).

### **6.6.3 Other considerations: medications**

For full information, see the manufacturer's Product Information (*Appendix 1*). Consideration should be taken with the co-administration of sulfasalazine with the following drugs:

- *Antacids* – Known to decrease the absorption of sulphonamides
- *Penicillins* – Sulphonamides may inhibit absorption and effectiveness of penicillins
- *Local anaesthetics derived from Para-amniobenzoic acid* – May antagonise sulphonamide activity
- *Digoxin* – Concomitant administration may cause reduced absorption of digoxin to sub therapeutic levels
- *Folic acid* – Folate deficiency may occur when taking sulfasalazine – co-administration of 1-2 grams daily of folic acid during pregnancy is recommended
- *Ferrous sulphate* – May inhibit the absorption and effectiveness of sulfasalazine
- *Azathioprine* – Bone marrow suppression and leucopenia have been reported with co-administration. Appropriate monitoring should occur with any co-administration.

## **7 STUDY ASSESSMENTS**

### **STUDY ASSESSMENTS PRIOR TO TREATMENT**

As part of routine clinical care, examinations and pathology tests will have been carried out prior to a participant's screening for recruitment. The results of these tests and examinations help to establish a patient's suitability for the study and give additional details that may be pertinent to the study analysis for stratification purposes. The following test and examination results will be transcribed as appropriate into the *Case Report Form* (CRF), following a participant consenting for inclusion in the study:

- Gravida and parity
- Estimated due date
- Height, weight and BMI at booking and at recruitment
- Blood pressure readings throughout pregnancy
- Medical progress notes tracking the history of the evolution of preeclampsia
- Pathology tests (including but not limited to *Full Blood Examination* (FBE); *Urea and Electrolytes* (U&Es); LFTs; Uric Acid; Oral Glucose Tolerance Test; coagulation profile; UA Dopplers; growth and wellbeing ultrasounds; etc.)
- Urine spot protein/creatinine ratio; and/or 24-hour urine collection
- First and/or second trimester dating ultrasound
- Aneuploidy screening tests
- Morphology ultrasound

#### STUDY ASSESSMENTS - DAY OF INITIAL TREATMENT DOSE

- Written, informed consent obtained
- Medical history review
- Discussion with participant's treating doctors and midwives
- Eligibility confirmed by senior member of the research team
- CRFs completed
- Sulfasalazine prescribed on medication chart by an obstetric doctor
- Assess for *Adverse Drug Reaction* (ADR) 30-180 minutes following administration of the initial dose
- At MHW only – Brachial artery flow-mediated dilatation measurements performed before first dose of sulfasalazine and after steady state has been achieved > 30 hours post commencing sulfasalazine.

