## **3 STUDY DESIGN**

This study is an early (phase II), unblinded, single-arm, proof of concept clinical intervention trial aiming to assess the safety and pharmacokinetic profile of sulfasalazine as a treatment for preterm preeclampsia.

20 participants with singleton pregnancies between 30+0 and 36+0 weeks gestation will be recruited over a two year period. Recruitment will occur at the Mercy Hospital for Women (15 participants) and Sunshine Hospital (5 participants) following a patient's antenatal admission to hospital with a diagnosis of proteinuric preeclampsia, as per the Society for the Study of Hypertension in pregnancy guidelines(1).

All recruited participants will receive 3 grams of sulfasalazine upon enrolment in the study. The following pathology tests will be collected in relation to the study:

Once the participant has been taking sulfasalazine for >30 hours:

- 6 x blood samples ( $\geq 5$  ml per sample collected in pink-topped plasma EDTA tubes) to assess maternal plasma levels and pharmacokinetics of sulfasalazine will be collected from the patient's dedicated intravenous cannula during one 12 hour period
- 3 x Mid-stream urine (MSU) samples ( $\geq 5$  ml per sample) to assess for maternal sulfasalazine excretion will be collected in one 12 hour period.

During remainder of pregnancy:

- When blood tests are collected as part of clinical care, an additional sample ( $\geq 5$  ml per sample collected in pink-topped plasma EDTA tube) will be collected to assess maternal serum biomarkers of preeclampsia including:
  - Anti-angiogenic factors associated with preeclampsia (sFlt-1 and sENG)
  - Biomarkers of endothelial injury (V-CAM, I-CAM and Endothelin)
  - 10 cytokine bioplex assay

Postnatally:

- Maternal blood (1 x pink-topped plasma EDTA tube), umbilical cord blood (1 x pink-topped plasma EDTA tube) and placental samples (6 x 30 g tissue samples) will be collected at delivery to assess for circulating sulfasalazine levels in both mother and baby

The hospitals' local Standard Operating Procedures (SOP) of managing preterm preeclampsia (including blood tests  $\geq 3$  times per week; twice weekly growth and wellbeing ultrasounds; *umbilical artery (UA) Doppler* and CTG monitoring 3 times per week) - or management as otherwise ordered by the treating obstetric unit – will be followed.

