### **4.2 INCLUSION CRITERIA**

Women who have/who are:

- A singleton pregnancy between 30+0 and 36+0 weeks at the time of treatment initiation
- Admitted as hospital inpatients with a diagnosis of preeclampsia as defined by the International Society for the Study of Hypertension in pregnancy guidelines(1)
- A pregnancy considered (by the treating obstetric unit) to be safe to continue for >12 hours after the time of recruitment
- Absence of major fetal anomalies identified on morphology ultrasound
- Aged 18-45 years at the time of recruitment
- Capable of understanding all study-related information presented to them (written, oral and electronic)
- Able to provide their written, informed consent to participate

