#### STUDY ASSESSMENTS - AFTER 30 HOURS OF SULFASALAZINE TREATMENT

- Insertion of a dedicated intravenous cannula
- Six blood ( $\geq 5$  ml collected in pink-topped plasma EDTA tubes each time) tests over one 12 hour period (via the cannula)
- 3 x MSU samples ( $\geq 5$  ml per sample, collected in yellow-topped sterile specimen pots) over one 12 hour period
- At MHW only – Repeated brachial artery flow-mediated dilatation measurements

After these specific samples and measurements are collected, study assessments will follow the pattern of normal clinical care as per local SOP for the treatment of preeclampsia. Study-specific blood samples ( $\geq 5$  ml collected in pink-topped plasma EDTA tubes) to assess for maternal serum biomarkers of preeclampsia will be collected along with any clinically indicated blood tests, as dictated by the treating obstetric team (usually every 2-3 days).

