### **9.2 PROPOSED ANALYSES**

Statistical analysis for this study will be performed using *GraphPad Prism 6* (GraphPad Software, La Jolla, CA). Given the study design and objectives of this particular trial:

- There is no comparison arm, so clinical variables and the clinical course will be presented as descriptive statistics
- There is no power calculation to perform
- Maternal and neonatal continuous variables will be statistically analysed using a t-test (parametric) or a Mann-Whitney test (non-parametric), as appropriate
- Categorical variables will be statistically analysed using a chi-squared test or Fisher's exact test, as appropriate
- Biomarker concentrations will be assessed as continuous variables
- Steady state sulfasalazine pharmacokinetic parameters will be estimated using standard non-compartmental techniques and normalized using actual body weights
- A p value of <0.05 will be considered statistically significant.

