#### **9.2.1 Primary outcome analysis**

- The primary objective of this study is to assess the safety of administering sulfasalazine in patients with preterm preeclampsia
- We will assess for adverse effects in the mother and the fetus/neonate
- We will assess mortality and morbidity outcomes - including neurological, respiratory, eye disorders and gastrointestinal disease - in the fetus/neonate
- We will also assess the pharmacokinetic profile of sulfasalazine which will involve taking maternal serum levels of sulfasalazine following administration; maternal urinary excretion of sulfasalazine following administration; and maternal serum levels, cord blood levels and placental levels of sulfasalazine at delivery
- Pharmacokinetic parameters include maximum concentration (C-max); time to maximum concentration (T-max); area under the concentration time curve (AUC); apparent oral clearance (CL/F); half-life; and renal clearance.

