## Pharmacokinetics

### *Absorption*

After the administration of a single 2 g dose of SALAZOPYRIN (enteric or non enteric coated tablets), sulfasalazine can be detected in serum within 6 hours. Two days after administration the serum concentration is negligible. With repeated daily doses, the steady state serum level of sulfasalazine is achieved after 4 to 5 days.

Sulfasalazine is poorly absorbed from the small intestine (up to 30%), after which it is excreted into the bile. A few percent of the given dose is excreted unmetabolised into the urine. The unabsorbed drug is excreted in the faeces. This is also confirmed by the observation that around 70% of an ingested dose of sulfasalazine can be recovered in the effluent of ileostomised patients. Sulfasalazine rapidly enters the enterohepatic circulation and is returned to the gastrointestinal tract via the biliary route. Up to 80% of the absorbed intact sulfasalazine can be recovered in the bile effluent.

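### PK sampled from just after 30 hours is labelled steady state although the appended Product Information says 4 to 5 days, and renal clearance is planned from urine specimens without volumes

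*Protocol*

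**What the plan says.** **Sampling time.** Protocol section 3 starts the PK collection "Once the participant has been taking sulfasalazine for >30 hours": six blood samples in one 12-hour period and "3 x Mid-stream urine (MSU) samples" of at least 5 ml each, also in one 12-hour period. Section 7 repeats this under "STUDY ASSESSMENTS - AFTER 30 HOURS OF SULFASALAZINE TREATMENT", and section 7.4 gives 30 hours or more after the first dose for the bloods.

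**Steady state.** In section 7 (day of initial treatment dose), the repeat flow-mediated dilatation is timed "after steady state has been achieved > 30 hours post commencing sulfasalazine". Section 9.2 applies the same idea to PK: "Steady state sulfasalazine pharmacokinetic parameters will be estimated using standard non-compartmental techniques and normalized using actual body weights".

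**Parameters.** Section 9.2.1 lists Cmax, Tmax and AUC, followed by "apparent oral clearance (CL/F); half-life; and renal clearance".

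**Appendix 1 (Product Information, Absorption).** "With repeated daily doses, the steady state serum level of sulfasalazine is achieved after 4 to 5 days". The same paragraph says that two days after a single 2 g dose the serum concentration is negligible.

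**Dosing.** Section 6.2 gives two equal doses a day, as evenly spaced as possible. Section 6.1.1 identifies the tablets as enteric coated.

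**The concern.** The pharmacokinetic profile is half of the primary objective (section 2.1.1). Apparent oral clearance taken as dose divided by AUC over one dosing interval is valid only at steady state. Before plateau, the interval AUC is too small and CL/F too large. The protocol's only PK source puts steady state at three to four times the sampling time (96–120 h against 30 h), and no reason is given for 30 hours.

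Renal clearance needs the amount of drug excreted over an interval, and the urine as specified does not supply it. This cannot be repaired at the analysis stage: volumes that were never recorded are lost, and section 7.4 has samples disposed of once processed.

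Section 7.1 also counts the measured serum levels among the safety assessments. Levels taken before plateau could understate later exposure. The repeat flow-mediated dilatation rests on the same assumption.

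**Working it through.** **Inputs from the protocol.** Sampling after more than 30 h (sections 3 and 7). Dosing interval about 12 h, so nominal doses at 0, 12, 24 and 36 h (section 6.2). Time to steady state 4 to 5 days, T = 96 or 120 h (Appendix 1). Serum level negligible 48 h after a single dose (Appendix 1).

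**Assumptions.** The documents give no half-life. I assume first-order accumulation with absorption fast relative to elimination, and that steady state means a fraction f = 0.90 to 0.97 of plateau. Slower absorption would lower the AUC fractions below.

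**1. Does 30 h reproduce as steady state?** Fraction of plateau at time t is 1 − 2^(−t/h), with h the half-life. For 30 h to give 90% or 95%, h must be at most 30 × ln2/ln(10) = 9.0 h or 30 × ln2/ln(20) = 6.9 h. The 4-to-5-day statement implies h = T × ln2/(−ln(1 − f)):

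- T = 96 h, f = 0.97: h = 19.0 h
- T = 120 h, f = 0.90: h = 36.1 h

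At these half-lives, 30 h gives 1 − 2^(−30/36.1) = 44% to 1 − 2^(−30/19.0) = 67% of plateau. So 30 h does not reproduce as steady state on Appendix 1's stated time.

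**2. Effect on AUC and CL/F.** AUC over the n-th 12-hour interval, relative to steady state, is 1 − 2^(−12n/h). CL/F is inflated by the reciprocal. The earliest interval that can be sampled in full after 30 h is the one following the fourth dose (36–48 h, n = 4):

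| Reading of Appendix 1 | h | AUC fraction, 36–48 h | CL/F overstated |
|---|---|---|---|
| 4 days = 97% of plateau | 19.0 h | 0.83 | 1.2-fold |
| 5 days = 90% of plateau | 36.1 h | 0.60 | 1.7-fold |
| 5% left at 48 h | 11.1 h | 0.95 | 1.05-fold |
| 1% left at 48 h | 7.2 h | 0.99 | 1.01-fold |

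The last two rows use the washout statement with h = 48 × ln2/ln(1/r), where r is the fraction remaining. What counts as negligible is again an assumption. On those rows 30 h is 85–94% of plateau.

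**3. Half-life.** A 12-hour window spans 12/36.1 = 0.3 to 12/19.0 = 0.6 of a half-life on the first reading, and 12/11.1 = 1.1 to 12/7.2 = 1.7 on the second. Appendix 1 also describes enterohepatic recirculation, and the tablet is enteric coated. Part of the window may therefore be absorption or recirculation rather than terminal decline.

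**4. Renal clearance.** CL_R = Ae/AUC, where Ae is the sum of concentration × volume over all urine passed in the interval. Three mid-stream specimens of at least 5 ml give concentrations only, and a mid-stream specimen is not a whole void. No section asks for void volumes or a complete timed collection, or says that the urine and blood periods coincide. The only 24-hour urine collection (section 7) is a routine pre-treatment test. For illustration, if 12-hour volume ranged from 300 to 1500 ml (assumed), the same concentration would correspond to amounts differing 1500/300 = 5-fold.

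**The case against.** Several points on the other side are fair.

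- **More than 30 hours is a floor.** Some profiles may be taken later, and a woman sampled on day 5 would meet Appendix 1's figure. But the protocol itself equates the floor with steady state and sets no later time.
- **Appendix 1 points two ways.** Its washout statement implies a shorter half-life and little bias, and the 4-to-5-day sentence gives no dose. This stands, and it is why the size cannot be fixed. It does not explain why the protocol departs from the one explicit time to steady state it contains.
- **The sentence that calls 30 hours steady state concerns flow-mediated dilatation at one site.** True, but sections 3 and 7 put the PK profile at the same point, and section 9.2 labels PK steady state directly.
- **Laboratory procedures not shown might call for urine volumes.** Possible. The protocol is silent rather than prohibitive, but it refers to no such collection, and a mid-stream specimen does not provide it.

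A reader might also infer more than the documents support. The sampling does not fail for every named parameter: six bloods in 12 hours can give an observed Cmax, Tmax and interval AUC. The window need not straddle a dose, since a 36–48 h profile complies. A two-fold error in CL/F would come from the 24–36 h interval, which cannot be sampled in full after 30 h. Eligibility requires only that the pregnancy is considered "to be safe to continue for >12 hours after the time of recruitment", so one might count women who deliver before a profile can be completed. The documents give no delivery times to support such a count, and section 9.1 does not promise 20 profiles.

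**Conclusion.** The point holds on two matters visible in the text. First, the protocol labels as steady state a PK profile that may start just after 30 hours, while its own appendix says 4 to 5 days, and nothing reconciles them. Second, renal clearance is a named parameter of the primary outcome analysis that the specified urine collection cannot yield; this needs no half-life assumption.

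The consequence for CL/F is conditional: about 1.2- to 1.7-fold overstatement if the 4-to-5-day figure governs, about 1–5% if the single-dose washout statement does. Both ranges assume first-order accumulation and a profile over 36–48 h. Half-life from this window is unreliable, more so on the longer readings. Cmax, Tmax and interval AUC remain usable as observed values at the actual sampling time.

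**What to change.** 1. Reconcile sections 7 and 9.2 with Appendix 1. Either justify more than 30 hours as steady state, or drop that label, report results by actual time since first dose, and describe CL/F and half-life as apparent. The flow-mediated dilatation wording needs the same correction.
2. Anchor the six blood samples to one dosing interval, from pre-dose to the next pre-dose, and record dose and sample times.
3. Collect all urine over that same interval with volumes and times, and compute renal clearance as amount excreted divided by AUC. Otherwise remove renal clearance from section 9.2.1.

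The non-compartmental method can stay. Assaying sulfasalazine in the EDTA plasma drawn later for biomarkers would show whether levels keep rising. It is optional, and useful only if time since last dose is recorded.

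The cost is recording dose times and void volumes, a protocol amendment with ethics committee approval (section 14.1), and a less favourable label if steady state cannot be justified. No dose or clinical rule changes.

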\* = Verbally confirm ongoing consent

\*\* = Maternal serum/urine levels taken following 30 hours of sulfasalazine therapy

\*\*\* = Maternal blood, placental and cord blood levels

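### The protocol calls a profile taken from 30 hours steady-state, but its own Appendix 1 gives 4 to 5 days, so AUC and CL/F from early profiles may be mislabelled and biased by an amount the documents do not fix

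*Protocol*

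**What the plan says.** Section 3 starts the six-sample blood profile "Once the participant has been taking sulfasalazine for >30 hours" and collects it within one 12-hour period. The footnote to Table 2 in Section 7.2 repeats the mark: "Maternal serum/urine levels taken following 30 hours of sulfasalazine therapy". Section 7.4 also uses 30 hours.

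Only one sentence says outright that 30 hours is steady state. It is in Section 7, under the day of the initial dose, and concerns the repeat flow-mediated dilatation measure at one site, taken "after steady state has been achieved > 30 hours post commencing sulfasalazine".

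Section 9.2 applies the same label to the drug profile: "Steady state sulfasalazine pharmacokinetic parameters will be estimated using standard non-compartmental techniques and normalized using actual body weights". Section 9.2.1 lists the parameters under the primary outcome analysis: C-max, T-max, "area under the concentration time curve (AUC); apparent oral clearance (CL/F); half-life; and renal clearance".

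Appendix 1 (Product Information, Pharmacokinetics, Absorption) says: "With repeated daily doses, the steady state serum level of sulfasalazine is achieved after 4 to 5 days". The sentence before it describes the serum concentration two days after a single dose as negligible.

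**The concern.** The protocol gives two times to steady state, 30 hours and 4 to 5 days, and does not explain why it sets the second aside. Dosing is twice daily (Section 6.2), so a woman has taken about three doses by 30 hours.

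The label matters because dose divided by AUC over one dosing interval equals CL/F only when accumulation is complete. Before that, AUC and C-max are too low and CL/F is too high. The pharmacokinetic profile is part of the primary objective (Section 2.1.1), and each woman has one multi-sample profile. The only later drug levels planned are those at delivery. If early profiles are reported as steady-state values, part of any apparent rise in clearance in preterm preeclampsia could come from sampling time. The second flow-mediated dilatation measure carries the same unsupported label.

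**Working it through.** **Inputs from the protocol.** Profile from 30 h, within one 12-hour period (Sections 3, 7 and 7.4). Two equal doses a day, taken as a dosing interval τ = 12 h (Section 6.2). Steady state after 4 to 5 days, that is 96–120 h, and a negligible level two days after a single dose (both Appendix 1).

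**Assumptions.** The documents give no half-life. I assume linear one-compartment kinetics with no absorption lag and elimination rate k, and vary k to match each Appendix 1 sentence. The first full dosing interval after 30 h follows the fourth dose, given at 36 h, so it runs from 36 to 48 h.

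**Can 30 h be reproduced?** No. It is 30/120 = 25% to 30/96 = 31% of the time in Appendix 1. The level reached at 30 h is 1 − exp(−30k) of plateau. For that to be 90–97%, the half-life would have to be about 9.0 to 5.9 h, a figure the protocol does not give.

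**Formula.** AUC over the n-th interval ÷ AUC at steady state = 1 − exp(−nkτ). For n = 4 this is 1 − exp(−48k), and CL/F is inflated by the reciprocal. The shortfall, exp(−48k), is also the fraction of a single dose left at 48 h.

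- *Reading A:* 4 to 5 days means that a fraction p of plateau is reached at time T. Then exp(−48k) = (1 − p)^(48/T).
- *Reading B:* negligible at two days means that a fraction r is left at 48 h. Then exp(−48k) = r.

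| Reading | Half-life (h) | Level at 30 h ÷ plateau | AUC 36–48 h ÷ steady state | CL/F inflation |
|---|---|---|---|---|
| A: 90% at 120 h | 36.1 | 0.44 | 0.60 | 1.66 |
| A: 90% at 96 h | 28.9 | 0.51 | 0.68 | 1.46 |
| A: 95% at 96 h | 22.2 | 0.61 | 0.78 | 1.29 |
| A: 97% at 96 h | 19.0 | 0.67 | 0.83 | 1.21 |
| A: 99% at 96 h | 14.4 | 0.76 | 0.90 | 1.11 |
| B: 10% left at 48 h | 14.4 | 0.76 | 0.90 | 1.11 |
| B: 5% left | 11.1 | 0.85 | 0.95 | 1.05 |
| B: 1% left | 7.2 | 0.94 | 0.99 | 1.01 |

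Worked example, first row: 0.10^(48/120) = 0.398, 1 − 0.398 = 0.602, and 1/0.602 = 1.66.

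The two Appendix 1 sentences meet only at a half-life of about 14.4 h, where inflation is 1.11. Longer half-lives strain the two-day sentence, and shorter ones strain the 4-to-5-day sentence.

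**Absorption lag.** With an assumed 3 h lag and absorption rate of 0.3 per hour, the AUC fraction falls to 0.55–0.78 for 90–97% of plateau under reading A, and to 0.86–0.98 under reading B. The direction does not change.

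**Later sampling.** For the interval starting at 96 h, n = 9. In the slowest case the AUC fraction is 1 − 0.10^(108/120) = 0.87, an inflation of 1.14. At 97% by 96 h it is 0.98, an inflation of 1.02. Women profiled then are largely unaffected.

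**Would a trough comparison show it?** The 12-hour level ÷ pre-dose level in the fourth interval is (1 − exp(−48k)) ÷ (1 − exp(−36k)):

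- half-life 36.1 h: 0.602/0.499 = 1.21
- half-life 14.4 h: 0.900/0.822 = 1.09
- half-life 7.2 h: 0.990/0.968 = 1.02

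The check is most informative where the bias is largest.

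**The case against.** The strongest reply is that the two-day sentence in Appendix 1 limits the bias. Under linear kinetics the AUC shortfall at 36–48 h is exactly the single-dose tail beyond 48 h, and Appendix 1 calls the level negligible by then. With 1% left, 30 hours is already about 94% of plateau and the label is nearly right. This stands as a limit on size. It does not remove the conflict, because the explicit statement about repeated dosing is still 4 to 5 days and the protocol does not choose between the two sentences.

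Three other points stand in part. The sentence that asserts steady state concerns flow-mediated dilatation, so the link to the drug profile depends on the shared 30-hour mark and on Section 9.2. The formula for CL/F is not stated and may sit in an analysis plan that is not shown, so the CL/F bias is conditional on dose over AUC for one interval. And 30 hours has a practical purpose: Section 4.2 requires only that the pregnancy be safe to continue for more than 12 hours, so later sampling would lose women who deliver early.

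A reader might infer that CL/F will be almost doubled, or that every woman's AUC is too low. The documents support neither. A near-twofold error needs a half-life of about 36 h, which would leave about 40% of a dose at 48 h and fits poorly with a negligible level. And 30 hours is a minimum, so women profiled after day 4 to 5 are little affected. A reader might also infer that profiles at 31 hours and at a week will be pooled, adding spurious variability. No upper limit is stated, but Table 2 has a dedicated 30-hour column ahead of later reviews, so wide scatter is conjecture.

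**Conclusion.** The inconsistency is real and reaches the primary pharmacokinetic parameters. If the plan is followed as written, profiles taken from 30 hours are reported as steady-state AUC and CL/F, although the appended Product Information says that steady state comes later and nothing in the protocol shows a plateau.

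For women profiled before day 4 to 5, any bias is one-sided under linear kinetics: AUC and C-max low, CL/F high. Its size is undetermined. Over 36–48 h CL/F is about 1.1 to 1.7 times too high on the 4-to-5-day sentence, and 1.01 to 1.11 times on the two-day sentence, given the one-compartment, 12-hourly, no-lag assumptions. It should be fixed. The sampling time itself is defensible, so this is a fault of labelling and reporting rather than of design.

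**What to change.** Reconcile Section 7, Section 9.2 and Appendix 1 on the time to steady state, either by justifying 30 hours or by removing the claim. Then:

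- Keep sampling from 30 hours so that early deliverers contribute, but call the result multiple-dose (about day 2–3) pharmacokinetics.
- Remove the steady-state label from the profile and from the second flow-mediated dilatation measure unless steady state is shown.
- Record hours since first dose and dose number for each profile. Dose times are already charted (Section 6.4).
- Make sure that the six samples include a pre-dose and a 12-hour sample, and compare them within the profile. Set in advance how close they must be to count as a plateau; a non-significant difference in so few women does not show one.
- Report AUC and CL/F as steady-state values only for women profiled at or after 4 to 5 days, or with a demonstrated plateau. Otherwise flag CL/F as likely biased upwards, or estimate it with an accumulation term.

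The cost is wording, two data fields and the placing of two samples already planned. No extra blood is drawn and no woman is lost. The downside is that fewer women will carry a steady-state value. Drug assays on the biomarker tubes could be added but are not needed, because those tubes are not timed to a dose.
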